**Figure 1 clc23231-fig-0001:**
[figure not shown]
Study design. AC, anticoagulant; AF, atrial fibrillation; NVAF, non‐valvular atrial fibrillation

Using the French National Health Insurance System (SNIIRAM) database, patients were identified and included in the study if they initiated a new anticoagulant treatment from 1 January 2014 to 31 December 31 2016. The study will be led by a project team, a coordinating center and a scientific board which is detailed in the Supporting Information Appendix 1.

Patients will be followed from the date of their first OAC prescription until the end of follow‐up, which is defined by the occurrence of a following event, whichever comes first:
*Switch to another anticoagulant treatment*: defined as dispensation of another anticoagulant molecule recorded after initiation of the studied anticoagulant treatment. Date of switch (and end of follow‐up) will be the date of the first dispensation of the other anticoagulant molecule.
*Discontinuation*: a patient who remains more than 30 days after the coverage by the last dispensation of studied anticoagulant treatment without refilling it will be considered as stopping this treatment. If a hospitalization occurs within this period, the length of the hospital stay will be deducted from the number of days without refilling of the treatment. For patients treated with VKAs, International Normalized Ratio testing realized during a hospitalization will be counted as a VKA dispensation. International Normalized Ratio testing will be used as a proxy of a VKA prescription only to extend VKA treatment exposure, but it will not be used as an index date. OACs drug coverages will be derived based on the recommended dosage, and the coverage of VKA treatment exposure will be defined as 35 days (ie, the median coverage time in days of VKA treatments, based on prior assessment on claims database). The median number of coverage days will also be calculated in the VKA patient population after data extraction.
*Last patient's health record*: defined by the last care (ie, consultations, dispensations, medical procedures…) recorded in the database before a period of 6 months without any reimbursed care. This includes situations like emigration and geriatric homes entry.
*Patient's death*.
*End of study period*.

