#### Secondary outcomes

3.4.2

For the secondary outcomes, the comparison between patients initiating apixaban and patients initiating each of the other anticoagulant treatments (dabigatran, rivaroxaban, and VKAs) will be performed only in the four sub‐cohorts of anticoagulant‐naive patients.

For all other descriptive objectives, the analyses will be performed in the eight sub‐cohorts.

Estimation by anticoagulant treatment and for both populations (anticoagulant‐naive and anticoagulant‐experienced patients) as follows:Quantitative variables will be described with the sample size, mean, standard deviation, median, interquartile range, minimum and maximum.Qualitative and ordinal variables will be described with the sample size and frequencies.

Analyses in anticoagulant‐naive and anticoagulant‐experienced populations as follows:The major characteristics of patients will be described for each anticoagulant treatment.Treatment patterns at anticoagulant initiation, over time, and concomitant treatment will be tabulated by anticoagulant treatment.Time‐to‐discontinuation will be estimated and plotted using cumulative incidence function by anticoagulant treatment.Healthcare resources utilization will be described by anticoagulant treatment.

For each endpoint of interest in the study, only the first evidence of its event will be considered in the analyses. Cox models have been chosen to align with the methodology used in other OAC publications. As this study has been conducted to address a specific request from French health authorities, the comparability of the methods with other OAC publication was an important contributor of the analytical choices made a priori.

Cox models or Fine Gray models are planned to be used in the analyses. The final choice of model will be based on the observed death rates, that is, in case of a high likelihood of competing risk of death, Fine Gray models will be used rather than Cox models.

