
Despite the numerous advantages related to the use of the SNIRAM database in pharmacoepidemiology studies, this database has limitations. First, there is a risk of incomplete data collection due to the research method using identification of patients through ICD‐10 diagnosis in the SNIIRAM database. Therefore, an algorithm needs to be applied to catch AF patients and can induce a diagnosis bias. Second, only major bleeding resulting in hospitalization is collected through PMSI. Less severe bleeding, requiring emergency care but no hospitalization will not be identified in the database. Third, due to the claim‐based retrospective nature of our study, treatment discontinuation of VKA could be biased due to the nature of individual variable dosing of VKA. Nevertheless, algorithms were performed to overcome these issues. In addition, as we used INR testing during hospitalization as a proxy for VKA dispensation, we might have miss patients who presented temporary interruption of their anticoagulant treatment. As the HAS requested clinical practice data documenting the therapeutic benefit of apixaban under actual conditions of use, compared with the standard oral anticoagulant treatment recommended in France (vitamin‐K antagonists, dabigatran, and rivaroxaban), only apixaban off‐label use were collected and therefore, off‐label data on other anticoagulants could not be reported. Fourth, one of the main limitations of this database, as is the case for many administrative databases, is the lack of information for certain clinical or biological risk factors for stroke, thromboembolism or bleeding. Without such information it is not possible to compare the distribution of these risk factors between anticoagulant treatments. Adjusting/matching for large numbers of covariates ascertain from patients' healthcare claims data improved control of confounding, as these variables could collectively be proxies for unobserved factors. Finally, future analyses of this study could also include complementary comparative approaches, such as using IPTW, which is another and probably better method to estimate an average treatment effect in the entire population if the treatment might be offered to every member of the population (ATE).

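### VKA coverage is one fixed 35-day median, so a continuing VKA patient can be recorded as stopped after 65 days; a sensitivity analysis with longer, data-derived coverage should be pre-specified

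*Protocol article*

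**What the plan says.** Section 3.1 of the protocol article (the follow-up rules after Figure 1) lists discontinuation among the events that end follow-up. The rule is common to all drugs: discontinuation applies to "a patient who remains more than 30 days after the coverage by the last dispensation of studied anticoagulant treatment without refilling it". If there is an admission in that period, "the length of the hospital stay will be deducted from the number of days without refilling of the treatment".

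The drugs differ in how coverage is obtained. In general, "OACs drug coverages will be derived based on the recommended dosage". For VKAs, "the coverage of VKA treatment exposure will be defined as 35 days (ie, the median coverage time in days of VKA treatments", a value taken from an earlier claims assessment that is not shown. VKA exposure can be extended in one further way: "International Normalized Ratio testing realized during a hospitalization will be counted as a VKA dispensation". The section adds: "The median number of coverage days will also be calculated in the VKA patient population after data extraction". It does not say whether the new median would replace 35 days.

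The rule feeds two sets of results. Section 3.2 lists persistence at 6 and 12 months, and section 3.4.2 says that time to "discontinuation will be estimated and plotted using cumulative incidence function by anticoagulant treatment". Follow-up for stroke or systemic embolism, major bleeding and death stops at the same date, and these outcomes are compared between apixaban and VKAs in anticoagulant-naive patients (section 2).

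The Discussion (section 4) concedes that "treatment discontinuation of VKA could be biased due to the nature of individual variable dosing of VKA" and says that algorithms were used to deal with it.

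**The concern.** A median describes the typical dispensation. It does not mark the point beyond which a patient has probably stopped. About half of VKA coverage times reach or exceed the median by definition, and for those patients the 30-day grace is partly or wholly taken up by tablets they still have. Where supply lasts beyond day 65, a patient who refills on time is still recorded as stopped.

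The two stated safeguards, deduction of hospital days and in-hospital INR tests, act only for patients who are admitted. A stable outpatient who uses packs slowly benefits from neither.

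Two results are at stake. The VKA time-to-discontinuation curve and the 6- and 12-month persistence figures could be shifted towards earlier stopping by the coverage rule itself. In addition, the VKA person-time behind the apixaban vs VKA comparisons would be shortened selectively, mainly among slow refillers without an admission.

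**Working it through.** **Inputs from section 3.1.** VKA coverage 35 days (a median). Permitted gap 30 days for all drugs. Other coverage from the recommended dosage. The 35 days cannot be reproduced, because the earlier claims assessment is not shown.

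**Assumptions.** The article does not say whether 35 days applies per dispensation or per pack; per dispensation is assumed. The spread of refill intervals is not given either. Intervals are taken as lognormal with median 35 days, with four pairs of between-patient and within-patient log-SD: 0.2/0.2, 0.3/0.2, 0.3/0.3 and 0.4/0.3.

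**Step 1: the implied cut.** 35 + 30 = 65 days after the last dispensation, or 65/35 = 1.86 times the median, before any hospital allowance.

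**Step 2: the same refill behaviour under the two coverage rules.** If coverage reflects a supply of Q days, the cut falls at Q + 30.

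| Supply, refilled on time | Cut if coverage = supply | VKA cut | VKA patient recorded as stopped? |
|---|---|---|---|
| 30 days | day 60 | day 65 | no |
| 60 days | day 90 | day 65 | no |
| 84 days | day 114 | day 65 | yes |
| 90 days | day 120 | day 65 | yes |

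**Step 3: share of single intervals above 65 days.** Total log-SD s = √(between² + within²), and P(interval > 65) = 1 − Φ(ln(65/35)/s), with ln(65/35) = 0.619.

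| Between/within | s | 0.619/s | P(interval > 65) |
|---|---|---|---|
| 0.2/0.2 | 0.283 | 2.19 | 1.4% |
| 0.3/0.2 | 0.361 | 1.72 | 4.3% |
| 0.3/0.3 | 0.424 | 1.46 | 7.2% |
| 0.4/0.3 | 0.500 | 1.24 | 10.8% |

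**Step 4: accumulation over a year.** 40,000 VKA patients who never stop were simulated for 365 days. Follow-up ends on day 65 of the first interval longer than 65 days. There are no admissions, switches or deaths.

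| Between/within | Falsely discontinued by 12 months | Person-time retained |
|---|---|---|
| 0.2/0.2 | 7.0% | 96.6% |
| 0.3/0.2 | 14.2% | 92.1% |
| 0.3/0.3 | 28.6% | 84.5% |
| 0.4/0.3 | 32.6% | 81.1% |

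Repeat runs agreed to within about half a percentage point. The loss is concentrated: 25% to 87% of the slowest-refilling quarter were falsely stopped, against at most 1.3% of the fastest.

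**Step 5: longer coverage.** The 90th percentile is 35·exp(1.282·s), which is 50.3 days at s = 0.283 and 66.4 days at s = 0.5. The cuts become about 80 and 96 days, so a true stopper stays exposed 15 to 31 days longer than under the 35-day rule. False discontinuation falls to 0.8%, 2.3%, 5.4% and 6.9% across the four spreads. The 75th percentile, 35·exp(0.674·s), is 42.4 to 49.0 days, which adds 7 to 14 days.

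**The case against.** The strongest case against the point has five parts.

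- **NOAC follow-up is cut too.** A reader might infer that NOAC patients face no such cut. Section 3.1 does not support that: the 30-day gap rule applies to every studied anticoagulant. Only the fixed coverage value is specific to VKAs. This objection stands.
- **The grace period absorbs most long intervals.** A reader might infer that half of VKA patients are misclassified because coverage is a median. They are not: intervals of 36 to 65 days are covered by the 30-day gap, and under the assumed spreads 89% to 99% of intervals fall within 65 days. This stands, although a small share per interval accumulates over a year of refills.
- **Lost person-time is not bias.** Losing exposed time unrelated to event risk costs precision and does not by itself shift a rate or hazard ratio. A reader might infer that the apixaban vs VKA results are biased in a known direction; the document gives nothing to show that. This stands. The persistence results are different, because the discontinuation date is itself the outcome there.
- **The limitation is disclosed, and detail may sit elsewhere.** The article condenses a fuller protocol, and sensitivity analyses are often left to an SAP. This stands in part. The article does fix the rule, and the only remedies it describes are the 35-day value, the in-hospital INR tests and the hospital-day deduction.
- **A longer coverage is a trade-off.** True stoppers would be counted as exposed for longer, and events off treatment would be attributed to VKAs. Observed intervals also include real interruptions, which inflate an upper percentile. This stands, and it argues against making the longer value the main definition.

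**Conclusion.** The point holds in a limited form. VKA discontinuation is judged at 65 days from a single median, while other coverage follows the recommended dosage. A continuing VKA patient whose next dispensation is later than that, with no hospital stay or in-hospital INR test in between, is recorded as stopped and leaves follow-up. This can bias VKA time-to-discontinuation and persistence towards earlier stopping, and it shortens VKA person-time selectively in the apixaban vs VKA comparisons. The direction and size of any effect on the stroke, bleeding or death hazard ratios cannot be determined from the document.

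Recalculating the median after extraction removes the problem only if the new value replaces 35 days and is materially longer. The article states neither.

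The 7% to 33% range for false discontinuation rests on the assumed lognormal shape, the chosen spreads, coverage per dispensation and the absence of admissions. If real refills cluster tightly around 35 days, the effect is small.

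**What to change.** The 35-day definition can remain the main one if the sponsor prefers it. Pre-specify a sensitivity analysis in which VKA coverage is a higher percentile, for example the 75th or 90th, of the VKA dispensation intervals observed after extraction, by molecule and number of packs where possible. Report VKA time-to-discontinuation and persistence, and the apixaban vs VKA results for stroke or systemic embolism, major bleeding and death, under both definitions. State whether the recalculated median replaces 35 days, and whether coverage is counted per dispensation or per pack.

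The cost is a few lines of text and one extra run on data already being extracted. In the sensitivity analysis, true VKA stoppers count as exposed for some extra weeks (about 15 to 31 days with the 90th percentile under the assumed spreads). The two definitions err in opposite directions and so bracket the error.

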#### Data source

3.1.1

The data source used for this study was the SNIIRAM database, which is the French national healthcare insurance system database with individual anonymous information of primary care and secondary care (hospital data from the French Hospital Discharge database [PMSI]), and it covers currently 98.8% of the country population. The SNIIRAM database contains a large number of variables, as previously described.^15^

The access to the SNIIRAM is regulated and requires approval from the “*Institut des Données de Santé*” (IDS, Institute of health data) and the “*Commission Nationale Informatique et Libertés*” (CNIL, the French data protection commission).

#### Study population

3.1.2

Patients will be included in the study if they are covered by the French national health insurance general scheme, with at least one reimbursement of anticoagulant treatment initiated with an index anticoagulant treatment (either naïve or experienced patients), aged 18 or older at their anticoagulant initiation, and diagnosed with AF in the 24 months prior the anticoagulant treatment initiation.

Patients will be excluded of the study cohorts if they had different types of anticoagulant treatment at the index date, diagnosed with a valvular condition in the 24 months before their anticoagulant initiation or treated for an indication other than stroke prevention in AF in the 6 weeks before their first anticoagulant reimbursement (including index date).

The study population will be identified in the database through consecutive steps as indicated in Figure 2 and detailed in Supporting Information Appendix 2.

**Figure 2 clc23231-fig-0002:**
[figure not shown]
Global flow chart of the study population. AC, anticoagulant; AF, atrial fibrillation; VKA, vitamin‐K antagonist

Anticoagulant‐naive patients will be defined as patients with no dispensation of anticoagulant treatment during the 24 months before the index date, and anticoagulant‐experienced patients corresponding to the others. Patients in the experienced group will only be included at their first entry. Therefore, all patients aged ≥18 years and covered by the French national health insurance general scheme, with at least one reimbursement for OAC treatments (VKAs, apixaban, rivaroxaban, or dabigatran) between January 2014 and December 2016, and without use of the same OAC in the 24 months before the index date (ie, date of the first dispensation) will be included. Only the first dispensation meeting this criterion determined the index date, that is, a patient could be included only once in the study.

Then, patients selected were allocated to four distinct sub‐cohorts of OAC‐naive patients (ie, with no dispensation of any OAC during the 24 months before the index date), receiving either VKAs, apixaban, rivaroxaban, or dabigatran during the study period. Anticoagulant‐experienced patients corresponded to the others.

### Study outcomes

3.2

Primary outcomes:
*Primary effectiveness outcome* will be the risk of stroke or systemic thromboembolic events which includes ischemic stroke, hemorrhagic stroke, and systemic thromboembolic events.
*Primary safety outcome* will be the risk of major bleeding which includes intracranial bleeding, gastric duodenal and rectum bleedings, acute posthemmorrhagic anemia, intraocular bleeding, otorrhagia, pericardic bleeding, respiratory bleeding, hemoperitoneum, intra articular bleeding, uterine and vaginal bleeding, and other major bleedings.

Variables used to capture effectiveness and safety outcomes are summarized in Table 1.

**Table 1 clc23231-tbl-0001:** Variables used for effectiveness and safety outcomes

Effectiveness outcome (risk of stroke and systemic thromboembolic events)	Safety outcome (risk of major bleeding)
**Identification of events (ICD‐10 codes collected in PMSI)** **– Ischemic stroke or not specified** Cerebral infarction (except cerebral infarction due to cerebral venous thrombosis, nonpyogenic): *code I63(except I636)* Stroke, not specified as hemorrhage or infarction: *code I64* **– Hemorrhagic stroke** Subarachnoid hemorrhage: *code I60* Intracerebral hemorrhage: *code I61* Other nontraumatic intracranial hemorrhage: *code I62* **– Systemic thromboembolic events** Arterial embolism and thrombosis: *code I74*	**Identification of events (ICD‐10 codes collected in PMSI)** **– Intracranial bleeding** Intracranial hemorrhage: *codes I60 to I62* Epidural hemorrhage: *code S064* Traumatic subdural hemorrhage: *code S065* Traumatic subarachnoid hemorrhage: *code S066* **– Gastric duodenal and rectum bleeding** Oesophageal varices with bleeding: *code I850* Gastro‐oesophageal laceration‐hemorrhage syndrome: *code K226* Gastric ulcer/duodenal ulcer/peptic ulcer/gastrojejunal ulcer with hemorrhage: *codes K250, K252, K254, K256, K260, K262, K264, K266, K270, K272, K274, K276, K280, K282, K284, K286* Acute hemorrhagic gastritis: *code K290* Hemorrhage of anus and rectum: *code K625* Hematemesis: *code K920* Melaena: *code K921* Gastrointestinal hemorrhage, unspecified: *code K922* **– Acute posthemorrhagic anemia**: ***code D62*** **– Intraocular bleeding** Retinal hemorrhage: *code H356* Vitreous hemorrhage: *code H431* Vitreous hemorrhage in diseases classified elsewhere: *code H450* **– Otorrhagia**: ***code H922*** **– Pericardic** Hemopericardium, not elsewhere classified: *code I312* **– Respiratory bleeding** Hemothorax: *code J942* Hemorrhage from respiratory passages: *R04* **– Hemoperitoneum**: ***code K661*** **– Intra articular bleeding** Hemarthrosis: *code M250* **– Uterine and vaginal bleeding** Recurrent and persistent hematuria: *code N02* Other specified abnormal uterine and vaginal bleeding: *code N938* Abnormal uterine and vaginal bleeding, unspecified: *code N939* Postmenopausal bleeding: *code N950* Unspecified hematuria: *code R31* **– Other bleeding** Hemorrhage, not elsewhere classified: code *R58* Traumatic secondary and recurrent hemorrhage: code *T792*

Abbreviations: ICD‐10, International Classification of Diseases, 10th Revision; PMSI, French Hospital Discharge database.

Secondary outcomes:Risk of occurrence of a composite morbidity criterion: unadjusted incidence rate in each sub‐cohort, composite morbidity criterion being defined by stroke, systemic thromboembolic events, and/or major bleeding, whichever occurs first.Risk of all‐cause mortality: unadjusted incidence rate of all‐cause death in each sub‐cohort.Major characteristics of patients and comorbidities, which are summarized in Table 2.Treatment patterns at anticoagulant initiation: Type of the prescriber initiating the anticoagulant treatment (general practitioners, office‐based cardiologists, hospital‐based physicians, and others), dispensed dosages, number of dispensed packaging at anticoagulant initiation, co‐prescription of dispensed treatments (other anticoagulants, antiplatelet agents, nonsteroidal anti‐inflammatory drugs, serotonin‐specific reuptake inhibitors, strong inhibitors of both CYP3A4 and P‐gp, HIV protease inhibitors, anticonvulsants, strong inducer of hepatic enzymes, and antiarrhythmic drugs) in each sub‐cohort.Treatment patterns over time:Adherence to treatment: Continuous Measure of Medication Acquisition version 7 (CMA 7).^16^
Persistence: number and percentage of persistent and non‐persistent patients over the 6 months and the 12 months after index date, time‐to‐event of persistence, median duration of persistence, number and percentage of non‐persistent patients with other anticoagulant therapy administered after discontinuation, during the gap, the number and percentage of persistent patients who had concomitant dispensings of other anticoagulant treatment over the exposure period of the studied anticoagulant, the number and percentage of non‐persistent patients who switched from studied anticoagulant treatment and re‐exposed after the switch during a 1‐year period, in each sub‐cohort.
Healthcare resources utilization description: use of medical visits, nurse acts, drugs packages delivered, biology acts, medical procedures, hospital stays, and sick leaves will be reported as:The number and percentage of patients with at least one reimbursement of a such healthcare resource use during the follow‐up period.The mean, SD, median, percentiles 10 and 90 of the number of care, only in patients with at least one reimbursement of the healthcare during the follow‐up period.

**Table 2 clc23231-tbl-0002:** Major patients characteristics and comorbidities evaluated for each anticoagulant

Sociodemographic characteristics: median age, sex ratio, region of residence, free‐access‐to‐care status
AF characteristics: time since AF diagnosis
LTD status distribution (LTD type, ICD‐10 code for diagnosis)
Previous hospital stay: number and total length of hospital stays
Previous exposure to anticoagulant treatment (class, molecule) over the three previous years, for anticoagulant‐experienced patients
Thromboembolism risk factors: CHADS2 mean score, CHA2DS2 VASc mean score, and distribution according to the scores
Bleeding risk factors: HASBLED mean score and distribution according to the score
Charlson mean score and distribution according to the score

Abbreviations: AF, atrial fibrillation; ICD‐10, International Classification of Diseases, 10th Revision; LTD, long‐term disease.

The study is registered at ClinicalTrials.gov, number NCT02640222. No other substudies have yet been planned.

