#### Primary effectiveness and safety outcomes

3.4.1

For primary effectiveness outcome, estimates by anticoagulant treatment and for both populations (anticoagulant‐naive and anticoagulant‐experienced patients) of:The number and percentage of patients presenting at least a stroke and/or a systemic embolic event during the 12 months after index date, and during the overall follow‐up period. This description will be also conducted by diagnoses sub‐division presented in Table 1.The unadjusted incidence rate: number of first event of stroke and/or systemic embolism by 100 person‐years and during the overall follow‐up period will be estimated by anticoagulant treatment. Person‐years are defined with the sum of follow‐up durations of the at‐risk population. The corresponding two‐sided 95% CI will also be represented using Poisson distribution.The time‐to‐event of first occurrence of stroke and/or systemic thromboembolism will be estimated and plotted using cumulative incidence function (the cumulative probability of failure from a specific cause over time) accounting for differences in follow‐up time and the competing risk of mortality (if mortality is greater than 10%). In the presence of competing risks of mortality, informative censoring of the observation time at death will be used, as mortality will be considered a competing risk for observing stroke and systemic thromboembolic events since patients who die before an event is observed cannot go on to have an event. In the absence of competing risks, the differences in follow‐up time will be accounted for through non‐informative censoring of the observation time at the end of follow‐up for each patient. Overall, the causes of censoring of each treatment group will be reported once the results will become available. Cumulative incidence curves will present the event risk over time (within first 12 months) for each newly initiated anticoagulant treatment while accounting for the competing risk of mortality (if needed) and differences in follow‐up time.Median duration to occurrence of first event of stroke and/or systemic thromboembolism: median duration (in days) between the index date and the date of the first studied event will be computed for patients with the event.

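### Table 1 files two hematuria codes under uterine and vaginal bleeding; counting I62 as hemorrhagic stroke is a definitional choice that merits sensitivity analyses

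*Protocol article*

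**What the plan says.** Section 3.2 defines the primary effectiveness outcome as a composite "which includes ischemic stroke, hemorrhagic stroke, and systemic thromboembolic events". It defines major bleeding through a list of sites that ends with "intra articular bleeding, uterine and vaginal bleeding, and other major bleedings". No urinary site appears anywhere in that list.

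Table 1 assigns ICD-10 codes to these components.

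- **Safety column, uterine and vaginal group:** N02 ("Recurrent and persistent hematuria"), N938, N939, N950 and R31 ("Unspecified hematuria").
- **Effectiveness column, hemorrhagic stroke:** I60 (subarachnoid), I61 (intracerebral) and I62 ("Other nontraumatic intracranial hemorrhage").
- **Safety column, intracranial bleeding:** "codes I60 to I62", plus the traumatic codes S064, S065 ("Traumatic subdural hemorrhage") and S066.

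For the number and percentage of patients with an event, section 3.4.1 adds: "This description will be also conducted by diagnoses", meaning by the sub-divisions of Table 1. It then applies the same methods to the safety outcome.

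**The concern.** **Hematuria.** Blood in the urine is not uterine or vaginal bleeding, and it occurs in men. Section 3.1.2 sets no restriction by sex, and Table 2 lists the sex ratio among the baseline characteristics, so the cohort contains both. A site table built on the Table 1 headings would show men with uterine or vaginal bleeds. Neither urinary nor gynecological bleeding could then be read off by anticoagulant.

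**I62.** By its label, this code holds the nontraumatic intracranial bleeds that are neither subarachnoid nor intracerebral. It counts towards both primary outcomes. The Introduction reports that NOACs reduced intracranial hemorrhage against warfarin in the randomized trials. An apparent effectiveness advantage, chiefly for apixaban against VKAs, could therefore partly reflect fewer bleeds in this residual code. A reader who sees only the composite could not tell.

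**Working it through.** The article gives no event count, code frequency or power figure that depends on these codes, so there is no stated figure to reproduce. The check compares labels with headings and follows each code into the outcomes that use it.

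**Step 1: labels against headings, safety column.** Of the five codes under uterine and vaginal bleeding, the labels of N938 and N939 name uterine and vaginal bleeding and that of N950 names postmenopausal bleeding. All three fit. The labels of N02 and R31 name hematuria and do not fit. The prose list in section 3.2 has the same uterine and vaginal site and no urinary one, so a lost heading in the typeset table does not explain the grouping.

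**Step 2: effect of regrouping.** Let S be the set of safety codes and E the set of effectiveness codes. The composite morbidity criterion counts the first event of either kind, so it uses E and S together.

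- Moving N02 and R31 to another heading within S leaves S unchanged, so total major bleeding is unchanged.
- E is untouched, so effectiveness and the composite are unchanged.
- Only the counts by sub-division change.
- The comparisons planned in section 2 cover stroke and systemic embolism, total major bleeding, all-cause mortality, baseline characteristics and resource use. None is by bleeding site, so no planned comparison changes.

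**Step 3: the rule behind I62.** Side by side, the two columns treat intracranial bleeds as follows.

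| Codes | Effectiveness | Safety |
|---|---|---|
| I60, I61, I62 (nontraumatic) | counted, as hemorrhagic stroke | counted |
| S064, S065, S066 (traumatic) | not counted | counted |

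This is a consistent rule: nontraumatic bleeds count in both columns, traumatic ones as bleeding only. I62 is treated exactly as I60 and I61 are.

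**Step 4: effect of leaving I62 out of E.** I62 stays in S, so major bleeding and the composite do not change. In the effectiveness outcome, patients whose only qualifying event is I62 drop out. Those with a later qualifying event stay in, with the later date. How many patients this concerns is not given.

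**The case against.** **On hematuria.** The codes are in the right outcome, major bleeding; only the sub-heading is wrong. Sub-division in section 3.4.1 could also mean the individual diagnosis lines of Table 1. N02, R31 and I62 would then each have their own row and the mislabelling would do little harm. Both points stand. They limit the error to descriptive tables and make it depend on how sub-division is read. They do not remove it, because the article does not settle the reading and the prose list in section 3.2 works at heading level.

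**On I62.** A reader might infer that I62 is misplaced because it is a bleed and not a stroke. The article does not support that. It gives no definition of stroke that excludes I62, and Table 1 applies one rule throughout. The Introduction does name intracranial hemorrhage separately from stroke or systemic embolism. But hemorrhagic stroke is itself intracranial bleeding, so that wording does not decide where I62 belongs. The overlap between the two primary outcomes is not peculiar to I62 either: I60 and I61 share it, as must happen when an effectiveness composite includes hemorrhagic stroke.

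A reader might also infer that I62 would supply about a third of any apparent effectiveness gain. That share comes from assumed inputs. Take VKA rates per 100 person-years of 1.50 for ischemic stroke or embolism and 0.40 for hemorrhagic stroke, of which 0.15 is I62, with hazard ratios of 1.00 and 0.45:

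- with I62: (1.50 + 0.45 × 0.40) / 1.90 = 0.884
- without I62: (1.50 + 0.45 × 0.25) / 1.75 = 0.921
- share of the gain: (0.921 − 0.884) / (1 − 0.884) = about 32%

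Rates of 1.2, 0.5 and 0.2 give 0.838 and 0.890, again about 32%. Changing one input of the first case moves the share:

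- I62 rate of 0.05: 0.884 with and 0.896 without, about 10%
- ischemic hazard ratio of 0.90: 0.805 with and 0.836 without, about 16%

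Every input here is an assumption. The range of 10% to 32% shows only that the answer follows from what is put in.

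**Conclusion.** The hematuria point holds on Table 1's own labels. N02 and R31 are grouped as uterine and vaginal bleeding, and reporting by heading would misdescribe them in both sexes. The consequence is confined to counts by bleeding site. It assumes that sub-divisions are the Table 1 headings and that no other document redefines the groups.

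The I62 point holds only as a request for transparency. Counting I62 as hemorrhagic stroke is a definitional choice, applied consistently and not shown to be an error, so the primary outcome need not change on this ground. Because the Introduction expects fewer intracranial bleeds on NOACs, the comparison against VKAs should show whether the effectiveness result depends on this code. No size can be attached to that dependence from the article.

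**What to change.** 1. In Table 1, create a urinary tract bleeding group for N02 and R31, and keep N938, N939 and N950 under uterine and vaginal bleeding. Add the urinary site to the list of major bleeding components in section 3.2.
2. State in section 3.4.1 whether sub-division means the headings or the individual diagnosis lines of Table 1.
3. Keep the primary effectiveness outcome as defined and add two sensitivity comparisons in anticoagulant-naive patients: one without I62, and one limited to ischemic or unspecified stroke plus systemic embolism (I63 except I636, I64, I74). Say briefly why I62 is counted as hemorrhagic stroke.

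The first two are edits to the code list and text, with no effect on the primary safety or composite totals. The third reuses codes that are already specified and costs a little more analysis work. The narrower outcomes will have no more events than the primary one, and so may be less precise.
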